# Study Procedures/Evaluations

## Study Procedures

The detailed design is outlined below and in the Appendices. Patients will be admitted to the Tasanh Health Center for the duration of study drug administration or until all signs and symptoms of malaria have disappeared, whichever comes later. Thereafter patients will regularly report for follow-up at least on Days 14, 21, 28, 35, and 42.

At the screening/baseline visit, the study will be fully explained to the subjects and written informed consent obtained. Subjects will be assessed as to whether they meet the inclusion/exclusion criteria. Demographic details (age, sex, weight, height) and medical history and concomitant medication details will be recorded. Vital signs (pulse, blood pressure, respiratory rate, and temperature) will be taken. A physical exam will be performed and clinical signs and symptoms will be evaluated. Blood smears to confirm *P. falciparum* malaria will be performed. Blood samples will be collected following the schedule outlined below.

Patient response to therapy will be monitored by assessing clinical parameters at baseline (Day 0) and daily at least until peripheral blood smears are negative for parasites. Specific detailed attention will be paid to daily (or more frequently if required) specified evaluation of any emerging adverse events including known potential toxicities that have been observed in human or animal studies with artemisinins. During hospitalization patients will have malaria smears performed up to 8 times on Day 0 and then every 6 hours until the smears are negative on 2 successive occasions. Thereafter blood smears will be performed on Days 14, 21, 28, 35, and 42. A final physical examination and blood testing may be requested from subjects who decide to withdraw from the study.

## Laboratory Evaluations

### Laboratory Evaluations/Assays

- Hematology (hematocrit, RBCs, WBCs, platelets) on days 0, 3, 6, and 14 (or whenever clinically warranted) (2 ml per blood draw).
- Glucose on days 0 (or whenever clinically warranted) (2 drops per blood draw).
- ALT on days 0, 3, 6, and 14 (or whenever clinically warranted) (1 ml per blood draw)
- Urine pregnancy test: Urine beta-HCG test. All female subjects will undergo a pregnancy test at baseline. Pregnant women will not be eligible for entry into the study.
- Urine (approximately 5ml) will also be collected from all participants to be frozen for probable antimalarial drug screening on the day 0 sample at a later date.
- Peripheral blood smears up to 8 times on Day 0 from blood drawn for other reasons or by finger prick blood smear at 12 and 18 hours and then 4 times daily until negative on 2 successive occasions. Thereafter blood smears will be performed on Days 14, 21, 28, 35, and 42 :
  - To determine species of parasite
  - To quantify parasitemia

### Special Assays or Procedures

- Blood samples for parasite DNA molecular marker characterization, parasite transcriptional expression profiling, and *in vitro* drug sensitivity will be collected on Days 0 and in case of re-emergence of parasitemia.
  - Samples for parasite DNA molecular marker characterization (8 ml each) will be collected to determine re-infection from recrudescence and to define molecular markers of drug resistance.
  - Samples for existing standard as well as novel new compounds in various stages of the drug development process *in vitro* drug sensitivity testing (8 ml each) will be collected and will follow the routine established at AFRIMS (Noedl 2004, 2005, and novel methodology and compounds).
  - Samples (5 ml each) for parasite total RNA will also be collected on Days 0 and in case of failure.
  - Samples for real time PCR analysis (up to 4 drops of blood per sample) to detect parasite densities below the microscopic detection limit will be collected every time a blood smear is made. These samples will be used to quantify parasitemia below the current level of detection of microscopy.
- Plasma samples for determining antimalarial drug levels (2 ml of whole blood per blood draw) will be collected from all patients on Day 0 just before and 15, 30, 60 (±10 minutes), 2, 4, 6 and 8 hours (±30 minutes) after drug intake, and again on Day 6 just before and 2, 4 and 6 hours after the final dose of artesunate.
- Plasma samples for bioassay (2ml) to evaluate any significant pre-study plasma antimalarial activity will be collected on admission prior to dosing and again if parasites reappear within the 42 day follow-up period.

### Specimen Collection, Preparation, Handling and Shipping

#### Instructions for Specimen Preparation, Handling, and Storage

Stained thick and thin blood smears will be examined by two microscopists who are blinded to each other’s results and to the treatment status of the study subject. Two blood smears will be made for every assessment. Slide 1 will be stained immediately and examined by a microscopist. The slide will then be stored together with the unstained slide 2 to be reexamined at a later stage. Parasite densities will be calculated based on a count of parasites per 200 WBCs (thick film) or per 5000 RBCs (thin film). A total of 200 oil immersion fields will be examined on the thick film before a blood smear is considered negative. The final count will be determined by taking the geometric mean of the two counts. In case of a difference in results (positive/negative; species diagnosis) between the two microscopists, the blood smear will be re-examined by a third microscopist and the third reading will be accepted as the final result.

Blood samples for parasite DNA molecular marker characterization will be collected in EDTA tubes and stored frozen at approximately -20ºC or below.

Blood for parasite RNA will be collected into PaxGene tubes and stored at room temperature or below.

Blood samples for *in vitro drug* sensitivity testing will be stored refrigerated if needed and the *in vitro* drug sensitivity assays will be performed directly at the study site. The remaining blood will be stored in liquid nitrogen for future drug sensitivity analysis.

The whole blood drawn for the measurement of drug levels (PK) will be collected, centrifuged, separated plasma and frozen at approximately -20ºC or below until testing. The frozen plasma will be stored at the study site and will be transported to AFRIMS laboratory in Thailand for analysis.

Specimens collected during the study will be labeled with the participants study ID number. Specimens will be stored for approximately 20 years at the Armed Forces Research Institute of Medical Sciences in Bangkok.

#### Specimen Shipment

The tests will be performed on site (*in vitro* drug sensitivity assay, microscopy, hematology, ALT, glucose, and urine pregnancy test) or at AFRIMS in Bangkok (PCR, drug screening testing, bioassay and pharmacokinetics) or at Center for Vaccine Development University of Maryland School of Medicine for parasite DNA molecular marker characterization and parasite transcriptional expression profiling and University of South Florida recovered parasite culture and *in vitro* drug testing. Specimens will be assigned new ID number by AFRIMS laboratory coordinator before shipping to the both collaborating laboratories for analysis.

## Rescue Treatment and Emergent *P. vivax* Infections

### Rescue Treatment

Subjects who fail to complete their randomly assigned artesunate dosing regimen for safety, tolerability, or other reasons, will receive treatment according to the following regimens to ensure adequate treatment of their *P. falciparum* malaria:

 If <3 doses of artesunate successfully given, patients will receive quinine/tetracycline in the following manner:

 If 3-5 doses of artesunate have been successfully administered, the patients will receive either mefloquine 15 mg/Kg orally + a second Mefloquine 10 mg/Kg oral dose administered 12 to 24 hours later, or Quinine/Tetracycline to complete at least 7 days of adequate antimalarial therapy if there is a contraindication to MQ (i.e. possible neurologic toxicity as the reason for stopping the artesunate). This will complete a standard ACT regimen (artesunate-mefloquine) or alternate adequate treatment regimen (quinine-tetracycline) for these subjects.

[figure not shown]

 If 6 or more doses of artesunate have been successfully administered, no further treatment is required.

All subjects receiving rescue treatment will continue to be followed until completion of their study periods (42 days) to ensure adequacy of treatment and appropriate safety follow-up.

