The artesunate will be administered orally (a single dose of 2, 4, or 6 mg/kg/day) over a total duration of 7 days (Day 0-6) with directly observed therapy.

Patients will be admitted to the hospital for the duration of study drug administration or until all signs and symptoms of malaria have disappeared, whichever comes first. After Day 6 they will be followed as Outpatients until Day 42 with scheduled follow-up visits on Day 14, 21, 28, 35, and 42.

Primary clinical outcome is cure (Adequate Clinical and Parasitological Response - ACPR) on Day 28 and 42 and the safety and tolerability of this previously untested experimental high dose (6 mg/Kg/D X 7 day, total 42 mg/Kg) artesunate monotherapy regimen. Secondary outcome measures are time until parasite, fever, and gametocyte clearance (PCT, FCT, and GCT). Parasite genotyping will be used to distinguish recrudescence from reinfection by PCR. Subjects will be monitored for clinical adverse events throughout the study duration.

Blood will be drawn on the day of admission (before initiating therapy) for *in vitro* drug sensitivity testing and for PCR (markers of drug resistance and to distinguish recrudescence from reinfection by genotyping). Malaria smears will be prepared regularly until parasite clearance and again at follow up visits on Days 14, 21, 28, 35, and 42 and whenever symptoms consistent with malaria appear. Plasma samples for determining drug levels will be obtained on the first and last day of therapy. Study participation for each individual will be 42 days.

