Once it develops and spreads, resistance to artemisinin derivatives, currently the most essential antimalarial drugs for the treatment of *Plasmodium falciparum* malaria, could very well be the most devastating event in the history of malaria control in the 21st century (Noedl 2005). Forty countries have officially adopted artemisinin-based combination therapy (ACT) for the treatment of malaria since 2001. Twenty alone have adopted the combination of artemether and lumefantrine as their first- or second-line treatment for *P. falciparum* malaria. Artemisinin and its derivatives are the most potent and rapidly acting antimalarial drugs. They reduce the infecting malaria parasite biomass by roughly 104 per cycle (White et al. 1999).

Currently used ACTs are starting to fail on both sides of the Cambodian-Thai border. In a recent study the efficacy of the combination of artesunate and mefloquine was reduced to only 79.3% with a 42-day follow-up in Pailin Province, in close proximity to our study site (Denis et al. 2006). Recent reports also suggest increasing numbers of failures with artemisinin combination therapies along the eastern borders of Thailand (Trat Province – data not PCR corrected), potentially due to artemisinin resistance (Vijaykadga et al. 2006). The authors report 21.4% failures in Trat Province with M5AS, a combination of 25 mg/kg mefloquine and 12 mg/kg of oral artesunate (as compared to only 3.4% in Tak province, along the Thai-Myanmar border, an area that is infamous for its high levels of drug resistance).

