# Artesunate: Efficacy and Safety Profile

Artesunate (AS) has been licensed for the treatment of malaria in many Southeast Asian countries since the 1990s. The drug is well absorbed, and rapidly hydrolyzed in the liver to the more active metabolite, dihydroartemisinin. Its half-life is less than 1 hour, so that all biological activity is gone after an oral dose within 12 hours (Teja-Isavadharm et al., 2001). While this drug is currently still considered to be the most potent blood schizonticide available, this rapid clearance requires repeated dosing of artesunate in order to clear all metabolically susceptible parasites. Generally artemisinin derivatives (artesunate and artemether) are extremely well tolerated when used at therapeutic dosage (Price et al. 1999).

Data from 23 trials with 1891 patients (Hien and White 1993) comparing artemisinin derivatives with other antimalarials showed shortening of fever clearance time compared to intravenous quinine and parasite clearance time by 17 and 32% respectively. Artesunate appeared to have more rapid action than the other derivatives. No serious toxicity was observed in these trials. 600 mg at 0 h and 4 h followed by 400 mg at 24, 32, 48 and 56 h was compared with oral quinine 1500 mg daily in 3 divided doses over 14 consecutive days, in patients with acute malaria. Shorter parasite and fever clearance times occurred in the artemisinin group but 50% of patients recrudesced compared with 23% in the quinine group. Monotherapy with artesunate is ineffective when given for 3 days or less. Li (1994) summarized the early Chinese data, reporting a recrudescence rate of 51% when artesunate monotherapy was administered for 3 days (total dose 280 mg-400mg) to 65 adults with uncomplicated falciparum malaria. Shorter regimens (total dose AS 600mg) given over 1-2 days did not cure any volunteers in Thailand (Bunnag et al. 1991). A subsequent randomized controlled trial by Li (1997) showed 39% recrudescence rate at day 28 with 400mg given over 3 days.

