**Standards of health care for acute uncomplicated *P. falciparum* malaria**

Standard of care (first-line therapy) for uncomplicated *P. falciparum* malaria is the combination of artesunate and mefloquine (Table 3).

*Table 3:* The combination of artesunate with mefloquine is the official first line therapy for adults in Cambodia; A+ M5 (artesunate + mefloquine, for 3days: artesunate 50 mg tablets and mefloquine 250 mg tablets (August 2007).

| Weight | Age | Number of Tablets | | | | | |
| --- | --- | --- | --- | --- | --- | --- | --- |
| Artesunate (50mg) | | | Mefloquine (250mg) | | |
| Day 1 | Day 2 | Day 3 | Day 1 | Day 2 | Day 3 |
| >35kg | >15 years | 4 | 4 | 4 | 2 | 2 | 1 |

The combination of quinine with tetracycline is the official second line therapy for adults in Cambodia. Both drugs are administered in split dose every 8 hours over 7 days (Table 4). In spite of the known side effects, particularly of quinine, this regimen is considered to be safe and highly efficacious.

*Table 4: Dosage of quinine (30mg/kg/24h) 300 mg tablets and tetracycline (25mg/kg/24h) 250 mg capsules for 7 days*

| Age | Weight  (kg) | Quinine | | | Tetracycline | | |
| --- | --- | --- | --- | --- | --- | --- | --- |
| Dose/8h | Total/day | Total/7days | Dose/8h | Total/day | Total/7days |
| <6 months | < 7 | 1/4 | 3/4 | 51/4 | - | - | - |
| 6m–2 years | 7-15 | 1/2 | 11/2 | 101/2 | - | - | - |
| 2-8 years | 16-30 | 1 | 3 | 21 | - | - | - |
| 9-15 years | 31-45 | 11/2 | 41/2 | 31½ | 11/2 | 41/2 | 31½ |
| >15 years | >45 | 2 | 6 | 42 | 2 | 6 | 42 |

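### The rescue rule treats an Arm 1 patient with 3 artesunate doses as having had a standard artesunate-mefloquine course, with about half of its artesunate

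*Protocol*

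**What the plan says.** Under Rescue Treatment, the choice of rescue depends only on how many artesunate doses were taken. Fewer than 3 doses leads to quinine/tetracycline, 3 to 5 doses to mefloquine 15 mg/kg plus 10 mg/kg, and 6 or more to nothing further. The visible text makes no distinction by arm and adds no artesunate. If mefloquine cannot be used, the 3-5 dose band allows "Quinine/Tetracycline to complete at least 7 days of adequate antimalarial therapy if there is a contraindication to MQ". The section then says of the whole band: "This will complete a standard ACT regimen (artesunate-mefloquine) or alternate adequate treatment regimen (quinine-tetracycline) for these subjects".

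The arms differ threefold in dose. The Protocol Summary gives "a single dose of 2, 4, or 6 mg/kg/day", and Table 7 confirms 2 mg/kg for Arm 1.

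The combination is described in two places. Table 3, the Cambodian first-line regimen, is "artesunate + mefloquine, for 3days: artesunate 50 mg tablets and mefloquine 250 mg tablets", with 4 artesunate tablets on each day for anyone above 35 kg. Background Information describes the Thai version as "M5AS, a combination of 25 mg/kg mefloquine and 12 mg/kg of oral artesunate".

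**The concern.** The purpose of the rule is to make sure that a patient who leaves the assigned regimen is still adequately treated. A count of doses does that only if a dose means the same amount in each arm, which it does not. A reader at the site would take the sentence as assurance that any patient with 3 doses, topped up with mefloquine, has had the national regimen. In Arm 1 that patient has not.

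There is also little margin in this area. Background Information reports that the "efficacy of the combination of artesunate and mefloquine was reduced to only 79.3% with a 42-day follow-up in Pailin Province", close to the site, so 100 - 79.3 = 20.7% were not cured on the combination itself. The sample size section assumes 80% cure in Arm 1 and 95% in Arm 3 over the same 7 days. That is a planning assumption, not evidence, but a rule that treats 6 mg/kg as a full standard course sits badly beside it.

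**Working it through.** **Inputs**
- Dose: 2, 4 and 6 mg/kg once daily in Arms 1, 2 and 3 (Protocol Summary; Table 7).
- National regimen: 4 tablets of 50 mg artesunate a day for 3 days; 2 + 2 + 1 tablets of 250 mg mefloquine (Table 3).
- Thai combination: 12 mg/kg artesunate, 25 mg/kg mefloquine (Background Information).
- Body weight: assumed 50 kg, implied by ARC1 (1400 mg for 28 mg/kg; 1400 / 28 = 50), with a range of 45 to 60 kg.

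**Reproducing the protocol's regimen**
- Artesunate: 4 x 50 x 3 = 600 mg; 600 / 50 = 12 mg/kg.
- Mefloquine: 5 x 250 = 1250 mg; 1250 / 50 = 25 mg/kg, the same as the rescue's 15 + 10.

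The two descriptions agree at 50 kg. The mefloquine part of the rescue is complete; only the artesunate part is in question.

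**Artesunate received before rescue (mg/kg = dose x number of doses)**

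| Doses | Arm 1 | Arm 2 | Arm 3 |
| --- | --- | --- | --- |
| 3 | 6 | 12 | 18 |
| 4 | 8 | 16 | 24 |
| 5 | 10 | 20 | 30 |

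Against 12 mg/kg, Arm 1 has 6/12 = 50%, 8/12 = 67% and 10/12 = 83%. Arms 2 and 3 have at least 100%.

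**Arm 1 against the fixed 600 mg of Table 3**

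| Doses | 45 kg | 50 kg | 60 kg | Weight at which 600 mg is reached |
| --- | --- | --- | --- | --- |
| 3 | 270 mg (45%) | 300 mg (50%) | 360 mg (60%) | 600/6 = 100 kg |
| 4 | 360 mg (60%) | 400 mg (67%) | 480 mg (80%) | 600/8 = 75 kg |
| 5 | 450 mg (75%) | 500 mg (83%) | 600 mg (100%) | 600/10 = 60 kg |

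An Arm 2 patient below 50 kg with 3 doses is also under the fixed amount (49 kg: 12 x 49 = 588 mg), but has had 12 mg/kg.

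**Does duration make up the difference?** Background Information ties artesunate's effect to the number of parasite generations exposed.
- 3 doses: 3 days, the same as Table 3. Nothing offsets the halved amount.
- 4 doses: one extra day, a partial offset.
- 5 doses: two extra days. Artesunate: Efficacy and Safety Profile reports 5% recrudescence with 440-600 mg over 5 days of artesunate alone, an amount that an Arm 1 patient of 440/10 = 44 to 600/10 = 60 kg has had. The offset is larger here, though a Thai series in the same section had 84% cure on 600 mg over 5 days.

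**The case against.** The strongest objection concerns the benchmark. The 12 mg/kg figure belongs to the Thai combination, whose artesunate, Background Information says, is given over only 2 days. The local standard is a fixed 600 mg with no per-kilogram floor: 10 mg/kg at 60 kg. A reader might infer from 6, 8 and 10 against 12 mg/kg that Arm 1 is under-treated across the whole 3-5 dose band. The documents do not support that. Against Table 3 the gap is gone at 60 kg after 5 doses and at 75 kg after 4, and below those weights extra days make up part of it. This objection stands and confines the error to 3 doses, where Table 3 itself is the comparator and 600 mg is reached only at 100 kg.

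A reader might also take the 3-day results as the risk after rescue: 51% recrudescence with 280-400 mg, and a second trial that "showed 39% recrudescence rate at day 28 with 400mg given over 3 days". Those patients had artesunate alone. Rescue adds full-dose mefloquine, and nothing in the protocol compares 300 mg with 600 mg over 3 days when mefloquine follows. Likewise, the Pailin figure describes the full combination, not the effect of less artesunate.

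A third inference would be bias between Arms 1 and 3. The protocol gives no basis for estimating how many Arm 1 patients would stop at exactly 3 doses, so neither its size nor its direction can be supported.

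The harm is limited. Dosing is observed in hospital, Arm 1 has the lowest dose, and ARC1 at twice that dose showed no artesunate toxicity and no serious adverse events. Smears continue to Day 42 with prompt retreatment. This keeps the point modest, but detecting a recurrence later is not adequate treatment at the time, and the sentence remains wrong for these patients.

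**Conclusion.** The statement that mefloquine completes a standard artesunate-mefloquine regimen is wrong for Arm 1 patients who stop after 3 doses. They have had 6 mg/kg, about half of the 600 mg that Table 3 gives over the same 3 days (45% to 60% at 45 to 60 kg). For Arm 1 with 4 or 5 doses the wording is loose rather than clearly inadequate. For Arms 2 and 3 the mefloquine rule is sound.

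This rests on two assumptions: body weights around 50 kg, and that the figure not shown in Rescue Treatment neither adds artesunate nor divides the rule by arm. It is a patient-care correction worth making because it is cheap. It does not touch the sample size or the primary test.

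**What to change.** Reword the 3-5 dose paragraph by arm and dose count:

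1. **Arm 1, 3 doses:** treat as for fewer than 3 doses. Give the full 7-day quinine/tetracycline course of Table 4 and do not count the artesunate days. Counting them would leave 7 - 3 = 4 days of quinine/tetracycline, and the protocol reports no results for that sequence. The full course has support: 100% 28-day cure in the ARC1 control group (95% CI 89.7 to 100).
2. **Arm 1, 4 or 5 doses:** keep the mefloquine rule. Replace the completion wording with a statement that the patient has had at least 4 days of artesunate plus full-dose mefloquine.
3. **Arms 2 and 3, 3 to 5 doses:** no change. Limit the completion wording to these arms.

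**Cost:** one paragraph, with no new drug, test, visit or weight table. A few Arm 1 patients, some of whom may have stopped for intolerance, would take a 7-day course dosed every 8 hours, with quinine's known side effects, instead of two mefloquine doses. If that course starts on Day 3 it runs to Day 9, three days past the planned Day 0-6 stay, so the site should say how those last doses will be supervised.

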### Treatment for emergent *P. vivax* infections

Enrolled subjects who develop *P. vivax* infection during the course of study follow-up will receive the usual Cambodian standard treatment for *P. vivax* consisting of oral chloroquine 25 mg/Kg divided over 3 days as well as treatment of *P. falciparum*. Currently primaquine is not recommended for radical cure within the Kingdom of Cambodia. These subjects will continue to be followed in the study until completion of their 42-day follow-up period for safety and efficacy.

